# The AvecNet Trial to assess whether addition of pyriproxyfen, an insect juvenile hormone mimic, to long-lasting insecticidal mosquito nets provides additional protection against clinical malaria over current best practice in an area with pyrethroid-resistant vectors in rural Burkina Faso: study protocol for a randomised controlled trial

**DOI:** 10.1186/s13063-015-0606-4

**Published:** 2015-03-25

**Keywords:** Insecticide resistance management, Malaria control, Insecticide-treated bed net, Pyrethroid, Pyriproxyfen, Insect juvenile hormone mimic, Clinical malaria, Entomological inoculation rate, Cluster randomized controlled trial

## Abstract

**Background:**

Recent reductions in malaria in sub-Saharan Africa have been associated with increased coverage with long-lasting insecticidal nets (LLINs). Pyrethroids are currently the only insecticide class used for treating nets, and the rapid increase in resistance to pyrethroids in vector mosquitoes may jeopardise future vector control. Nets containing a novel combination of permethrin, a pyrethroid, and pyriproxyfen, an insect juvenile hormone mimic, (PPF-LLIN) may enhance malaria control, as well as reducing the spread of pyrethroid-resistant mosquitoes. This trial will determine whether PPF-LLINs provide incremental protection against malaria over current best practice of LLINs and prompt treatment in an area with pyrethroid-resistant vectors.

**Methods:**

A 2 armed cluster-randomised controlled trial will be conducted in Burkina Faso to assess whether PPF-LLIN (containing 2% permethrin and 1% pyriproxyfen w/w) provide better protection against clinical malaria in children than 2% permethrin-treated LLINs. Study subjects will be recruited and provided with LLINs at the start of the study. The LLINs will be exchanged for PPF-LLIN by cluster in a step-wedge fashion so 3 months before the end of the 2 year trial all participants will have a PPF-LLIN. The primary endpoint will be clinical malaria incidence measured by passive case detection in a cohort of children, aged 6 months to 5 years. Anaemia and parasite prevalence will also be measured in children during cross-sectional surveys. Exposure to malaria parasites will be assessed using light traps followed by identification of common vector species and their sporozoite infection rates. Safety evaluation will include recording of adverse events and pregnancy outcomes. The main endpoint analysis will include adjusting for distance between village clusters with different types of nets, as the impact of PPF-LLIN is likely to increase as larger areas are dominated by PPF-LLIN, reducing the spill over of mosquitoes from villages with LLINs.

**Discussion:**

The step-wedge design is to measure the impact of an incrementally delivered environmental intervention where we expect the degree of control to be improved as more people use PPF-LLIN over a larger area. Trial findings will help inform policy makers on the effectiveness of PPF-LLIN nets for malaria control in areas of pyrethroid resistance.

**Trial registration:**

ISRCTN21853394 – AvecNet, registered on 3 April 2013.

**Electronic supplementary material:**

The online version of this article (doi:10.1186/s13063-015-0606-4) contains supplementary material, which is available to authorized users.

## Background

Enormous progress has been made in the control of malaria in sub-Saharan Africa over the past decade [1,2]. A significant part of this achievement has resulted from a large-scale increase of long-lasting insecticidal net (LLIN) distribution and indoor residual spray campaigns, both interventions being extremely successful tools for malaria control [3,4]. Nonetheless, the future success of these programmes is threatened by the development of insecticide resistance in the vectors [5]. Resistance is of particular concern since, until now, bed nets can only be treated with pyrethroids because of their rapid knockdown activity, high mosquito mortality ability and extremely low toxicity to humans [6,7]. Thus, although an intact bed net is protective as a physical barrier [8,9], tolerance of malaria vectors to pyrethroids would dramatically reduce the protection afforded by LLINs.

In order to increase the effectiveness of LLINs, net treatments are being developed where nets are treated with a pyrethroid in combination with another active ingredient, such as pyriproxyfen [10,11]. Pyriproxyfen is an insect juvenile hormone mimic that is recommended for vector control by the World Health Organization (WHO) because it is effective at extremely low concentrations, is safe for people [6], and has no cross resistance with other classes of insecticide used for vector control. Its primary effect is to prevent metamorphosis of pupae into adults. In addition, it can sterilise adult mosquitoes, or at least reduce their fecundity and longevity [10,12-15]. Pyriproxyfen has good residual activity in fresh water, with studies on mosquito control showing that it can be effective for 5 to 9 months after initial treatment [16,17].

Polyethylene nets treated with a combination of permethrin and pyriproxyfen (PPF-LLIN; trade name Olyset Duo (Sumitomo Chemical, Japan),) have been shown to induce higher mortality and reduce blood feeding of pyrethroid-resistant *Anopheles gambiae* s.s. than permethrin-only LLINs (Olyset) in experimental hut trials [11]. However, no controlled study demonstrates that PPF-LLIN will provide incremental protection against malaria beyond the current best practice of LLIN and prompt treatment in a controlled trial. Building on current best practice, the present trial aims to measure the incremental impact of PPF-LLIN on clinical malaria in communities using LLINs alone and having access to rapid treatment. To achieve this we will conduct a cluster randomised controlled trial in rural villages to the south-east of Banfora town in Burkina Faso, a country where malaria is relatively stable [18]. Mosquitoes in this area are currently increasing in resistance to pyrethroids. In 2010 in Tiefora, located at the edge of our trial zone, there was resistance to 1,1,1-trichloro-2,2-di(4-chlorophenyl) ethane (DDT) (12% mortality), permethrin (48% mortality) and deltamethrin (39% mortality) ([name], personnel communication).

Here we describe the proposed trial design and the methodology used. Although some of the outcome measurements and methods in this protocol are based on a previous vector control trial conducted in West Africa [19], the nature of the intervention and setting have led to many novel features.

### Study objectives

#### Clinical

##### Primary objective

To assess whether PPF-LLIN provide added protection against clinical malaria in children compared with pyrethroid-only LLINs over 2 malaria transmission seasons of follow-up.

##### Secondary objectives

ᅟ

### Efficacy

To assess whether PPF-LLIN provide added protection compared to LLINs against anaemia and/or parasite prevalence in children.To assess and compare the prevalence of microscopy-confirmed gametocyte carriers in the LLIN group versus the PPF-LLIN group.

### Safety

To assess whether PPF-LLIN have a safety profile comparable with conventional LLINs in the trial population.

#### Entomological

##### Primary objective

To assess whether PPF-LLIN reduce the entomological inoculation rate (EIR) of mosquitoes collected inside houses compared to LLINs.

##### Secondary objectives

To assess whether PPF-LLIN reduce pyrethroid resistance in the vector population.To assess the impact of PPF-LLIN on *Anopheles gambiae* and *Anopheles funestus* on egg production and the survival of the larvae that emerge from these eggs.

## Methods/Design

### Study area and participant eligibility

The study site is situated south of the road from Banfora and Sideradougou (10° 56’ 00” N, 004° 46’ 00” W) and is approximately 1,250 km^2^, bisected by a river in a north-south axis. It is an area of West Sudanian savannah and the climate consists of a rainy season from May to October with little rain in other months. This defines the seasonal malaria transmission with most malaria episodes experienced during or immediately following the rainy season. The study area has 6 health centres and every village is affiliated to only 1 health centre. A baseline demographic survey conducted in July 2013 enumerated 63,903 individuals living in 93 villages, with most people living in small rural villages in houses made with mud or cement walls and thatched or metal roofs. The study’s field station is based at Banfora town which is the main town in the district. This study is in an area of cotton growing since 1968 with both the S and M forms of *An. gambiae* s.s. [20].

Each village or groups of neighbouring villages with more than 50 children aged 6 months to 5 years old will be invited to join the study, and will constitute a single cluster. Following local custom, sensitisation will start by discussions with community elders and then with representatives of the whole study community in order to explain the nature and requirements of the study. Village level permission will then be sought after sensitization meetings attended by village community leaders and health staff at the health centres; attendees’ names and village of residence will be documented. Witnessed written consent will also be sought from each net recipient, before net donation and exchange (Additional file 1). During these procedures it will be made clear that people will be able to leave the study at any time but that their original net will not be returned.

A cohort of children will be enrolled to assess the impact of the intervention on malaria. A minimum of 40 children per cluster (range 40 to 75), depending on cluster size, will be randomly selected, stratified by age and invited to participate in the clinical and travel/residence surveys and passive case detection (PCD). The random sample will be stratified by age so that approximately equal numbers of children below and above 36 months will be invited into the study. This was done in case there were marked differences in clinical malaria associated with the different age groups and to ensure balance between the 2 study arms. No distinctions in the sampling scheme will be made regarding gender, ethnic group, medical condition or physical health. Children will only be included on the condition that their carers/parents give witnessed informed written consent. Assurance will also be sought from carers/parents that they expect that the child will remain resident in their village during the transmission season and will not be sent away. If informed consent is not provided for a randomly selected child then replacement children will be randomly selected from those remaining in the village.

The impact of the intervention on the density of malaria vectors and their infection rate with malaria sporozoites will be measured in each village cluster. In each cluster 6 compounds will be selected randomly, from those that have consented to join the study and have at least 4 houses. In each household a room with a single adult male sleeper will be selected if the room owner/sleeper provides witnessed, verbal consent.

### Design

A cluster-randomised controlled trial design will be used since: i) LLINs are a community-level intervention; and ii) the village cluster is a suitable unit for randomization since they represent a discrete spatial cluster. At the outset of the study, all households will be provided with new LLINs at the rate of 1.1 nets for every 2 people in their household; this will approximate 1 for every sleeping place. Each month for the next 4 months after LLIN donation, residents in 5 randomly selected village clusters will be asked to exchange their LLINs for PPF-LLIN. Stratified, random sampling will be used to ensure that by the end of year 1 (September 2014) there will be a similar number of residents with and without PPF-LLINs affiliated to each health centre. Every month from June to September in 2015, an additional 5 village clusters will be provided with PPF-LLIN, thus by the end of September 2015 all clusters will have PPF-LLIN (Figure 1). It is important that within the study area there are no villages that are not enrolled in the study in order for the PPF-LLIN to have maximum impact on larval populations and minimize the spill-over of mosquitoes from villages without these nets. LLINs and PPF-LLIN will be the same shape, size and colour and marked with a unique code number, so that the investigators are blinded to the identity of the net (apart from those field assistants distributing nets).

**Figure 1 Fig1:**
[figure not shown]
**Step-wedge design for roll-out of bednets.** Permethrin-treated nets were given to all clusters in May 2014, followed by pyriproxyfen & permethrin treated nets (red) being rolled-out to different clusters in 2014 and 2015.

Clinical malaria will be recorded by study nurses using PCD methods during the rainy seasons in years 1 and 2. Parasites will be detected by rapid diagnostic tests (RDTs) and thick smears will be stained for confirmation and parasite counting by study staff. Treatment will follow government guidelines.

The study cohort will be surveyed for malaria indices (parasite prevalence, anaemia and spleen rate) at the beginning and end of both transmission seasons to generate data for the secondary endpoints. Where possible, at each malaria survey except the first, an average of 50 children from each village cluster who have not been enrolled in the cohort but are of a similar age will also be surveyed for these malaria indices. This additional group of children may better reflect the *Plasmodium falciparum* parasite rate in the population than children in the PCD cohort. Baseline data from the cohort will be used to compare the village clusters before the interventions, and the cohort from each village cluster provides its own baseline data before net exchange to PPF-LLIN. In addition, we will request anonymized medical records from the 6 health facilities located in the valley and use these to document clinical malaria in children aged 6 months to 5 years living in villages outside the study area. These children represent a further control group which can be used to track temporal changes in malaria incidence during the study period. If malaria declines in the study area in year 2, but not outside, we can be confident that the decline is due to the intervention, rather than confounding factors such as low rainfall. The end-of-season survey data will also be used to attempt to define a *P. falciparum* parasitaemia cut-off giving optimum sensitivity and specificity for malaria cases in this setting [21].

A schematic representation of the trial is shown in Figure 2.

**Figure 2 Fig2:**
[figure not shown]
**Schematic representation of the trial.**

### Randomisation

In cluster-randomised controlled trials it is particularly important to minimize imbalance for factors known to be highly correlated with the disease outcome - in this case age and location. In each cluster, children will be enrolled with equal numbers of children aged 6 to 35 months and 36 to 60 months, and children who drop out of the study in year 2 will be replaced, as far as possible, by children of a similar age. At each step of the wedge, clusters will be selected, as far as possible, to maintain an even balance of children in the 2 age groups. Balanced randomization will be used to ensure that, within each health centre catchment area, half of village clusters will have PPF-LLIN and half LLINs by the end of July 2014.

Stratified randomisation of village-cluster to the trial arms, as outlined above, will reduce some imbalances between these but, as only a relatively small number of units can be randomized in such a cluster design, it is important to assess baseline levels of malaria and known confounders. Baseline data parasite rates and anaemia collected from enrolled children in each cluster in May 2014 will be used to assess imbalances in malaria at the village-cluster level.

Observer bias will be reduced where feasible. Both types of nets will be of a similar shape and colour. As well as using RDTs, blood films will be read by microscopists blinded to the identity and intervention status of the subjects. Mosquito collector bias will be reduced by using standard Centers for Disease Control and Prevention (CDC) miniature light traps, which do not rely on the ability of the fieldworker to collect specimens. Trap catches will be examined by a different person to the trap collector and they will be blinded to the trap location and intervention status. The processes of the intervention, both for PPF-LLIN and LLINs, will be monitored closely not only for quality but also to document any bias between the clusters.

### Interventions

#### Long-lasting insecticidal nets

The LLINs are manufactured by Sumitomo Chemical (Japan). These are WHO recommended and meet WHO specifications with 2% w/w permethrin incorporated into polyethylene fibres giving adequate release of permethrin for about 5 years. These nets will be distributed at the beginning of the main transmission season, at no cost to the recipients. We will use white ‘extra family’ size rectangular nets (180 cm wide × 190 cm long × 150 cm high) of a white colour throughout. Government Roll Back Malaria information, education and communication procedures will be followed to encourage correct net use and maintenance, including supplying the nets in individual pre-opened bags.

LLINs will be stored locked at ambient temperature in Banfora, under the control of a delegated individual, ready to be moved to the Health Facilities in batches by lorries and held by the officers in charge before being transported to the villages for distribution by the study team. In advance of distribution, the number of beds/sleeping places and the number with LLINs will be counted. New nets will be exchanged for old nets at the household level to achieve one LLIN per bed/sleeping place. Net use by study children will be monitored during the monthly travel/residence surveys during the 2014 and 2015 transmission seasons.

#### Permethrin and pyriproxyfen long-lasting insecticidal nets

PPF-LLIN will be provided by Sumitomo Chemical (Japan) and are currently undergoing evaluation by the WHO Pesticide Evaluation Scheme. The nets contain 2% w/w permethrin and 1% w/w pyriproxyfen incorporated into polyethylene fibres giving adequate release of permethrin and pyriproxyfen for an estimated 3 years (decay rates of the insecticides on PPF-LLIN are similar to those of LLINs over 6 months, unpublished data). The PPF-LLIN will be the same size and colour as the LLINs and will be distributed the same way, but this distribution will be to the first 5 village clusters 1 month after the LLIN distribution and will be rolled out in a wedge-shaped design at monthly intervals during the main transmission season in 2014 and 2015. PPF-LLIN will be stored and distributed in a similar manner to the control LLINs.

### Clinical data collection and patient treatments

PCD for malaria will be maintained during the transmission seasons in 2014 and 2015 (June to December 2014, and June to December 2015). Parents/guardians will be encouraged to take their child to the health facility their village is affiliated with at any time their child becomes unwell. The cost of travel and treatment for sick children will be met from the study funds. Study nurses will work in close collaboration with the government health workers to monitor malaria cases as indicated above. Project fieldworkers will visit each nurse regularly, at least once a week, to record children with malaria episodes.

The end of transmission season survey in December 2015 will be the final study visit for the enrolled children in the cohort and will be similar to the end transmission season survey in 2014.

During the course of the study participants are free to receive medication from health personnel outside the study team but they are encouraged to use their allocated health facility. During the clinical surveys, sick children, those with anaemia (haemoglobin (Hb) <9 g/dL), diagnosed malaria or any other mild illness will be referred to their health facility. Children with severe malaria, or other serious conditions, will be referred to Banfora or Sideradougou Health Centres for treatment.

For safety considerations (see section below) we will identify asthmatic residents in study villages by name, household and village. During distribution and follow-up of PPF-LLIN in 2014 and 2015 these residents will be checked weekly by trial nurses for any aggravation of their symptoms for the first month after net donation and at the end of this month they will ask these residents to contact the study team if they have cause for concern. We will also identify pregnant women in study villages from antenatal clinic records, from June 2014 onwards, and outcomes of pregnancies will be recorded onto data forms, including miscarriages, live/still birth, weight and any recorded malformations. The regular monthly demographic surveillance system (DSS) in trial villages will also include reports of miscarriages. Data on asthmatics and pregnancy outcomes will then be linked to the date of reception of PPF-LLIN to examine if the events are associated with PPF-LLIN.

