### Safety considerations

Although adverse events (AEs) arising from either net are highly unlikely, we will document their safety in a community setting, by recording AEs and serious adverse events (SAEs) in the study cohort and population for the duration of the study. The trial will follow standard definitions for AE and SAE agreed by consensus of the Collaborating Centres of the WHO International Drug Monitoring Centre (Uppsala, Sweden). The occurrence of AEs will be sought by non-directive questioning of the study children at monthly visits during the trial. AEs will also be recorded if volunteered by study children or their parent/carer or are noted by nurses through physical examination, laboratory test, or other assessments at any contact with the participant; these will be recorded on the child’s CRF for that visit. All AEs such as skin rashes, respiratory problems, streaming eyes, and so forth, will be recorded with the grade of severity (mild, moderate or severe).

In addition, we will record pregnancy outcomes for all resident pregnant women, and asthma signs/symptoms in pre-identified asthmatic residents, as indicated in the clinical data collection and patient treatments above.

During the course of the study, SAEs will be captured using a specific SAE report form and within 2 days of the start of the SAE, field staff will deliver a completed SAE report to the study physician. The study physician will log these in a query book noting the child’s study identification number or the residents demographic surveillance system number and village of residence and report these to the Principle Investigator who will inform the responsible member of the trial Data and Safety Monitoring Committee. Excessive grouping of SAEs by clusters will be reported to the study’s Data Monitoring and Ethics Committee and Trial Steering Committee.

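### As described, asthmatic residents are actively checked only in the month after PPF-LLIN receipt, so an asthma excess cannot be told apart from closer observation

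*Protocol article*

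**What the plan says.** The secondary safety objective is comparative: "To assess whether PPF-LLIN have a safety profile comparable with conventional LLINs in the trial population".

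The section on clinical data collection and patient treatments gives the only asthma schedule. Asthmatic residents are identified by name, household and village, and then: "During distribution and follow-up of PPF-LLIN in 2014 and 2015 these residents will be checked weekly by trial nurses for any aggravation". The checks run "for the first month after net donation and at the end of this month they will ask these residents to contact the study team" in case of worry, so they give way to self-report. The use of the data is also stated: "Data on asthmatics and pregnancy outcomes will then be linked to the date of reception of PPF-LLIN to examine if the events are associated"; the association meant is with the PPF-LLIN.

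The Safety considerations section adds no further asthma schedule. It refers back: "asthma signs/symptoms in pre-identified asthmatic residents, as indicated in the clinical data collection and patient treatments above". The same section does commit to recording adverse and serious adverse events throughout the trial, in the cohort and in the wider population, and it names respiratory problems as an example. Its active element covers the cohort only: "The occurrence of AEs will be sought by non-directive questioning of the study children at monthly visits during the trial".

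**The concern.** How hard asthma is looked for changes on the same date as the exposure. Before exchange, and in clusters still on LLIN, no one is described as asking asthmatic residents in general about aggravations. On receipt of a PPF-LLIN a nurse asks weekly for a month, and then active asking stops. If the net does nothing, events would still tend to cluster just after receipt, because that is when someone is asking.

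Two errors are possible. The trial could raise a false alarm about a net that the Discussion says has not been evaluated in the field beyond small hut studies. Or a real signal could be dismissed as an artefact, because the data offer no way to tell the two apart. Analysis cannot repair this afterwards: aggravations that no one asked about under LLIN are not in the dataset.

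**Working it through.** The article gives no asthma figure, so there is none to reproduce. Two things can be worked out: how actively checked time divides between the nets, and what ratio unequal searching could produce by itself.

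**1. Schedule.** "Permethrin-treated nets were given to all clusters in May 2014" (Figure 1 legend); call May 2014 month 0. The Design section has 5 clusters exchanging in each of the next 4 months (months 1 to 4) and 5 in each month from June to September 2015 (months 13 to 16). The last survey is in December 2015 (month 19), which gives 20 months. Clusters: 5 × 8 = 40.

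**2. Time under each net.**
- LLIN: 5 × (1+2+3+4+13+14+15+16) = 5 × 68 = 340 cluster-months.
- PPF-LLIN: 40 × 20 − 340 = 460 cluster-months.

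**3. Time under weekly checks.** One month per cluster after exchange gives 40 cluster-months, all PPF-LLIN, and 0 of the 340 LLIN cluster-months. The checked share of PPF-LLIN time is f = 40/460 = 0.087. Of those 40, 35 (7 steps × 5 clusters) fall in months when other clusters are still on LLIN. Concurrent comparators therefore exist for all but the last step, but they are not asked the same questions.

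**4. Ratio with no true effect.** Let a be the probability that an aggravation is recorded under weekly checks, and p the probability otherwise. Then:
- first month after receipt against LLIN: a/p
- all PPF-LLIN time against LLIN: 1 + f(a/p − 1)

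The documents give neither a nor p. Assumed ranges are a = 0.8 to 1.0 and p = 0.2 to 0.8.

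| a | p | First-month ratio | Ratio over all PPF-LLIN time |
|---|---|---|---|
| 0.8 | 0.8 | 1.0 | 1.0 |
| 0.8 | 0.4 | 2.0 | 1.09 |
| 0.9 | 0.4 | 2.25 | 1.11 |
| 0.8 | 0.2 | 4.0 | 1.26 |
| 1.0 | 0.2 | 5.0 | 1.35 |

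The last column takes p as equal under LLIN and in later PPF-LLIN months. The plan invites residents to come forward at the end of the checked month and describes no such invitation under LLIN. If that raises later self-report, the ratio over all PPF-LLIN time would be larger.

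**5. A contrast within the same paragraph.** Pregnant women are identified from antenatal records from June 2014 onwards, and the monthly demographic surveillance system (DSS) also reports miscarriages. Neither is triggered by the type of net. Of the two special safety groups, only the asthmatic residents have active follow-up tied to PPF-LLIN.

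**The case against.** Four points can be made on the other side.

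- **There is a comparator.** A reader might infer that asthma has none. The documents do not support that: adverse events are recorded population-wide under both nets, and study children are questioned monthly under both. What is missing is a comparator of equal intensity for asthmatic residents in general. This point stands and limits the claim.
- **An excess need not be an artefact.** A reader might also infer that any excess would come from ascertainment. That does not follow. A true effect could contribute, and the assumed ranges include a ratio of 1.0. Over all PPF-LLIN time the distortion is modest. This point stands too.
- **The wording may be looser than it looks.** The phrase about net donation is unqualified, and the Design section speaks of donation for the first LLIN distribution. However, the sentence opens by restricting itself to PPF-LLIN distribution and follow-up in 2014 and 2015, and no LLIN distribution is planned for 2015. The PPF-LLIN reading is the natural one; if the other was meant, the text should say so.
- **No asthma endpoint or estimator is fixed, and the full protocol may hold more.** It is true that asthma is not among the listed endpoints. But the article does state both a collection rule and a use of the data to examine association, and the difficulty lies in how those two combine, not in missing detail.

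Season is not a separate flaw. All exchanges fall in June to September, but clusters are randomised to steps, so concurrent LLIN clusters could deal with season if ascertainment were equal.

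**Conclusion.** The point holds in a limited form. As described, weekly checks cover about 40 PPF-LLIN cluster-months and none of about 340 LLIN cluster-months, so linking asthma events to PPF-LLIN receipt confounds type of net with intensity of search. An early excess could not be separated from closer observation. The bias runs towards apparent harm from the PPF-LLIN, but its size is unknown: the figures of 1.0 to 5.0 for the first month and about 1.0 to 1.35 over all PPF-LLIN time rest wholly on assumed detection probabilities.

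This concerns one part of a secondary safety objective. The primary endpoint and the listed secondary endpoints are untouched. It should be corrected, since the remedy is small.

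**What to change.** Leave the weekly checks as they are, as individual safety monitoring, and report their findings descriptively. State which net donation starts them.

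For the comparison of nets, use only data gathered the same way under both. Add one fixed asthma-aggravation question for the listed residents to the existing monthly DSS contact, in every cluster whatever its net, from June 2014. As the article appeared in March 2015, any rounds already completed without the question cannot be recovered, and it should start with the earliest round still possible. Compare PPF-LLIN with LLIN within calendar month, and leave events found only by the weekly checks out of the comparative rate. Both nets are in use concurrently until the last step in September 2015.

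The cost is one question for a list of named residents, plus protocol wording. Monthly recall is coarser than weekly checks, and recent weekly visits may still prime some answers. The article does not confirm that the DSS contact reaches these residents in person; if it does not, some extra visits would be needed.
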